## Methods/Design

### Trial Design

Members of the community with elevated levels of depressive symptoms were randomised in a 2 by 2 quasi-factorial design to receive either the ISG, the ITP, a combination of the ISG and IPT or a plausible internet-based attention control (IAC) (see Table 1). Measures were administered at screening, baseline, post-test, and 6 and 12 months after the intervention commencement.

**Table 1 T1:** Quasi-factorial trial design and target sample sizes per cell.

	Internet support group (ISG)		
**Automated skills training program (ITP)**	**No ISG**	**ISG**	**Target total**

**No ITP**	125 (IAC)	125	250

**ITP**	125	125	250

Target total	250	250	500

Approval to conduct the trial was granted by The Australian National University Human Research Ethics Committee (Protocol 2007/2259). The study protocol is registered with the Controlled Clinical Trials registry (ISRCTN65657330).

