### Planned data analysis and sample size

The WellBeing trial aimed to recruit and randomise 500 participants to four conditions (125 per group). The primary analysis will be undertaken on an intent-to-treat basis. Mixed-model repeated measures (MMRM) analyses will be used because this method has been demonstrated to be superior to using the last observation carried forward method for handling missing data in longitudinal designs [52]. For analyses of categorical outcomes, non-linear mixed modelling methods will be used. Based on previous studies, [8] we estimated pre-post effect sizes for the automated training program, the attention placebo and the ISG to be .6, .1, and .35 respectively. Power was set at 80% and calculations conservatively assumed a correlation of .5 between pre- and post-test measurements. Under these conditions the target sample size could detect a change from baseline of approximately .25 standard deviations in *a priori *contrasts of treatment arms conducted within the framework of omnibus test of condition by time mixed model repeated measures analysis. It is planned that the unique effect of the combined treatments will be tested by appropriate contrasts. It is possible that the combinations of treatment (e-couch and ISG) will prove no better than the individual programs. Conversely, cumulative effects or potentiation (synergy) may be observed. The target sample size ensured that the study is powered to detect an effect of .25 in either direction.

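### The detectable effect of .25 SD at 80% power does not hold for pairwise contrasts of two arms of 125: on pre-post change, power at .25 is about 51% and the 80% detectable difference is about .35 SD

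*Protocol article*

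**What the plan says.** All the power statements are in the protocol article, section Planned data analysis and sample size. The trial "aimed to recruit and randomise 500 participants to four conditions (125 per group"). The assumptions are these: "Power was set at 80% and calculations conservatively assumed a correlation of .5 between pre- and post-test measurements". From them the article concludes that "the target sample size could detect a change from baseline of approximately .25 standard deviations in" comparisons between arms that were specified in advance. These comparisons are to be made inside an overall condition-by-time test from the repeated-measures model.

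The expected effects are also given: "we estimated pre-post effect sizes for the automated training program, the attention placebo and the ISG to be .6, .1, and .35 respectively".

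The section then raises the possibility that the combined intervention is no better than its components, or that the two reinforce each other. It ends: "The target sample size ensured that the study is powered to detect an effect of .25 in either direction".

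Two other places bear on the reading. Table 1 under Trial Design ("Quasi-factorial trial design and target sample sizes per cell") shows 125 in each cell and margins of 250. Objectives of the ANU WellBeing study asks for ISG and ITP each against IAC, for the three active conditions against one another, and for the combination against each single program. The sample-size section does not mention pooling over the margins.

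**The concern.** At a correlation of .5 the SD of the pre-post change equals one baseline SD. The standard error of a difference in change between two arms of 125 is then too large for .25 SD to be detected with 80% power. The stated figure is what one obtains with twice as many people per side, or with no comparison group at all.

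This matters because .25 is the plan's own expected difference for two of the comparisons in the objectives: ISG v IAC (.35 − .1) and ITP v ISG (.6 − .35). A reader who takes the paragraph at face value would credit both with 80% power. The same holds for combined versus single programs, where the closing sentence repeats the figure.

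**Working it through.** **Inputs from the protocol article.** n = 125 per arm; margins of 250 v 250 (Table 1); power 80%; correlation ρ = .5; pre-post effects of .6 (ITP), .1 (IAC) and .35 (ISG).

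**Assumptions.** Alpha and sidedness are not stated. I take two-sided 5%, which fits the closing reference to an effect in either direction, and also try one-sided 5%. I assume complete data and no multiplicity adjustment; both favour the plan.

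**Step 1: scale.** In baseline SD units, SD(change) = √(2(1 − ρ)) = √(2 × .5) = 1. Baseline-adjusted at one post-test, SD = √(1 − ρ²) = √.75 = .866.

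**Step 2: formulas.** Power at .25 = Φ(.25/SE − 1.960). The 80% detectable difference = (1.960 + .842) × SE = 2.802 × SE.

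**Step 3: reproduce the plan's figure.**
- Pooled main effect, 250 v 250, on change: SE = √(2/250) = .0894. Detectable difference = 2.802 × .0894 = .251. Power at .25 = Φ(2.795 − 1.960) = 79.8%.
- Within-arm change, n = 125: SE = 1/√125 = .0894, so again .251 and 79.8%.

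**Step 4: pairwise contrast, 125 v 125, on change.**
- SE = √(2/125) = .1265.
- Power at .25 = Φ(1.976 − 1.960) = 50.7% (50.4% with the noncentral t).
- Detectable difference = 2.802 × .1265 = .354 SD.
- n per arm for 80% at .25 = 2 × 2.802²/.25² = 251.2, so 252.

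**Step 5: alternatives and the other contrasts, 125 per arm.**

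| Contrast and analysis | SE | Power at .25 | 80% detectable |
|---|---|---|---|
| Pairwise, change, one-sided 5% | .1265 | 63.0% | .315 |
| Pairwise, baseline-adjusted, single post-test | .866 × .1265 = .1095 | 62.6% | .307 |
| Pairwise, mean of three post visits minus baseline (ρ = .5 throughout) | .816 × .1265 = .103 | 67.7% | .289 |
| Pairwise, baseline-adjusted mean of three post visits (ρ = .5 throughout) | .645 × .1265 = .082 | 86.5% | .229 |
| Combined v mean of the two single arms, change | √(1.5/125) = .1095 | 62.6% | .307 |
| Interaction (difference of differences), change | √(4/125) = .179 | 28.7% | .501 |

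**Step 6: the plan's own effects, pairwise, on change.** ITP v IAC (.6 − .1 = .50): 97.7%. ISG v IAC (.25) and ITP v ISG (.25): 50.7% each.

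**The case against.** The strongest defence is that the figure is right for a contrast the design supports. The trial is described as a 2 by 2 quasi-factorial, Table 1 prints margins of 250, and a factorial main effect is itself a linear contrast of the four arms. For that contrast .25 is correct to rounding. This stands, so it would be too strong to say that .25 is wrong for every contrast of arms. It does not rescue the paragraph, because the objectives also set pairwise comparisons and the closing .25 claim concerns the combination against its components. A comparison of margins cannot answer that.

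A second defence is the repeated-measures model. CES-D is measured at three post-baseline points, and a baseline-adjusted average over them would exceed 80% power at .25 (86.5%). So it cannot be said that no analysis open to the plan reaches 80% with 125 per arm. But the calculation as described rests on pre-post effect sizes and a single pre-post correlation, and no time-averaged contrast is mentioned.

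Nor can the origin of .25 be fixed with certainty. One arm against the other three, baseline-adjusted, has SE √(.75 × (1/125 + 1/375)) = .0894 and gives the same value.

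Third, alpha is not stated, so 51% and .35 SD depend on the two-sided 5% assumption. A one-sided 5% test raises power only to 63%.

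Finally, recruitment is complete, so correcting the sentence cannot change the sample. That limits the remedy to the wording; it does not make the stated figure right.

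**Conclusion.** The point holds for pairwise contrasts. On the stated inputs, with two-sided 5% and complete data assumed, two arms of 125 have about 51% power at .25 SD on pre-post change, and the 80% detectable difference is about .35 SD (63% and .31 SD if baseline-adjusted at one post-test). The closing claim also fails for the combination: a pairwise comparison with one program has the same 51%, a comparison with the mean of the two has 63%, and the synergy contrast has 29%. Dropout or multiplicity adjustment would lower these figures.

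A reader might infer that the trial as a whole is underpowered, or that a null ISG result is bound to be misread. The documents do not support either. ITP v IAC has about 98% power at its assumed difference of .50, and the pooled ISG main effect has about 80% at .25 if there is no interaction. How a null result would be interpreted is speculation. What is established is that a single figure is attached to contrasts for which it does not hold.

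**What to change.** Revise the power statement in Planned data analysis and sample size as follows.

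1. State the contrast, alpha, sidedness and analysis model behind .25.
2. Report about .35 SD as the 80% detectable difference for pairwise arm contrasts on pre-post change (about .31 SD if baseline-adjusted at a single post-test), with the alpha and complete-data assumptions alongside.
3. Limit .25 SD to the pooled factorial main effects (250 v 250), assuming no ISG-by-ITP interaction.
4. Withdraw the closing claim of power for .25 where it refers to combined versus individual programs.

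The cost is a less favourable stated figure. The analysis does not change and no further enrolment is needed. I would not add a pooled ISG test as part of this correction. That would be a new analysis choice, and an arguable one: the section on the combined intervention says that arm used a separate board with an additional forum, so the two ISG cells did not receive identical support groups.

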### Objectives of the ANU WellBeing study

The primary objectives of the study are to (i) evaluate the efficacy of a depression Internet Support Group (ISG) and an automated psychoeducational and skills Internet Training Program (ITP) for reducing depressive symptoms relative to a plausible Internet Attention Control condition (IAC); to evaluate the relative efficacy of the ITP, ISG and combined ITP and ISG interventions; and (iii) to ascertain if the adherence rates and magnitude of improvement in depressive symptoms is greater for the ISG and ITP interventions combined than for either condition alone.

Secondary objectives of the study are to (i) evaluate the effect of the two experimental interventions on anxiety, disability, social support, loneliness, self-esteem, empowerment, loneliness, depression literacy, stigma and help seeking in people with elevated depressive sympotms; and (ii) to compare the outcomes of these interventions in rural and metropolitan residents.

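### The .25 SD power statement does not hold for the combined arm: combined versus one single program has about 51% power at .25, and .25 suits the interaction only on an unstated half scale

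*Protocol article*

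**What the plan says.** All references are to the Protocol article. Under Trial Design, participants were "randomised in a 2 by 2 quasi-factorial design", and Table 1 gives 125 per cell and 250 per margin. Under Planned data analysis and sample size, the trial "aimed to recruit and randomise 500 participants to four conditions (125 per group"). For the power calculation, "Power was set at 80"%, and "calculations conservatively assumed a correlation of .5 between pre- and post-test measurements". On these inputs the sample "could detect a change from baseline of approximately .25 standard deviations in" a priori contrasts of treatment arms.

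The section then turns to the combined arm. Its unique effect is to be tested by contrasts that are not written out. The combination might turn out no better than the single programs; alternatively, "cumulative effects or potentiation (synergy) may be observed". The next and last sentence is: "The target sample size ensured that the study is powered to detect an effect of .25 in either direction".

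The combination is a primary question. Objective (iii), under Objectives of the ANU WellBeing study, asks whether the "magnitude of improvement in depressive symptoms is greater for the ISG and ITP interventions combined than for either condition alone".

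The section states no alpha, no dropout allowance and no separate calculation for the combined arm.

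**The concern.** Coming straight after the hypotheses about the combination, the closing sentence reads as a power claim for them. Those hypotheses rest on cells of 125. Combined versus one program compares two cells, and synergy involves all four. A figure that is right for margins of 250 cannot simply be carried over.

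What is at stake is how a null result is read. A reader told that the trial was powered for .25 could take a non-significant combined-versus-single comparison as good evidence that adding one program to the other gains less than .25 SD. If true power at .25 is near one half, that inference is not available from the test alone.

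**Working it through.** **Inputs from the article:** 125 per arm; power 80%; pre-post correlation .5; assumed pre-post effects of .6 (ITP), .35 (ISG) and .1 (control).

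**Assumptions not in the article:** two-sided alpha 5% (the phrase about either direction suggests two-sided); analysis of a single pre-post change; no dropout; normal approximation.

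**SD of change**, in baseline SD units: √(2(1 − .5)) = 1.0. With baseline adjustment instead, the residual SD is √(1 − .5²) = .866.

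**Formulae:** power = Φ(effect/SE − 1.96); detectable effect at 80% power = (1.96 + .84) × SE.

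**1. Reproducing the plan's figure**
- Factor main effect, 250 v 250: SE = √(2/250) = .0894; .25/.0894 = 2.80; power 79.8%; detectable effect .25.
- Within-arm change, n = 125: SE = √(1/125) = .0894; the same 79.8% and .25.

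So .25 is correct for these two quantities.

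**2. Combined versus one single program, 125 v 125**
- SE = √(2/125) = .1265; .25/.1265 = 1.98; power 50.7%; detectable effect .354.
- Baseline-adjusted: SE = .866 × .1265 = .1095; power 62.6%; detectable effect .307.

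**3. Interaction as a difference of differences**, combined − ITP − ISG + IAC
- SE = √(4/125) = .179; .25/.179 = 1.40; power 28.7%; detectable effect .501.
- Baseline-adjusted: SE = .866 × .179 = .155; power 36.5%; detectable effect .434.

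**4. The same interaction on a half scale**, mean(combined, IAC) − mean(ISG, ITP)
- SE = √(1/125) = .0894; power 79.8% at .25. But .25 on this scale is 2 × .25 = .50 as a difference of differences, so this agrees with step 3.

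**5. Sensitivity, power at .25 SD**

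| Variant | Combined v one program | Interaction (difference of differences) |
|---|---|---|
| Base case | 51% | 29% |
| One-sided 5% | 63% | 40% |
| Baseline-adjusted and one-sided 5% | 74% | 49% |
| Two-sided 1% | 27% | 12% |
| Change to mean of three follow-ups, all correlations .5 | 68% | 40% |
| Baseline-adjusted mean of three follow-ups, all correlations .5 | 87% | 58% |
| Correlation .7, change score | 72% | 44% |
| Correlation .8, change score | 88% | 60% |
| 20% dropout | 42% | 24% |
| 40% dropout | 33% | 19% |

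**6. The plan's own assumed effects.** If effects relative to control add, the combined arm reaches .6 + .35 − .1 = .85. Its advantage over ISG alone is then .50 (98% power), but over ITP alone it is .85 − .60 = .25 (51% power). An effect of .25 is therefore what the cumulative scenario implies against ITP.

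**7. Precision.** The 95% CI half-width for combined minus one program is 1.96 × .1265 = .248. For illustration, an observed advantage of .10 would be non-significant, with an interval from −.15 to .35, and so compatible with a true .25.

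**The case against.** Four counter-arguments deserve weight.

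**The contrast and its scale are not given.** The article writes down no coefficients. On the half scale, both main effects and the interaction have 79.8% power at .25, which matches the stated figure and fits the wording about either direction. A reader might infer from the 29% that the power claim for synergy is a plain miscalculation. The documents do not support that: 29% holds for the difference of differences, and the article does not say which scale it used. What stands is that the scale must be stated, because .25 on the half scale means a synergy of .50 SD. The half scale does nothing for combined versus one program.

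**The planned analysis may do better than one change score.** The plan is a mixed model with three post-baseline CES-D assessments, and it calls the .5 correlation conservative. With a correlation of .8, or with baseline adjustment on the average of three follow-ups, combined versus one program passes 80%. These cases show that 51% is a base case and not the power of the final analysis. But the article rests its claim on a pre-post correlation of .5 and a change from baseline, and under those conditions 125 v 125 does not reach 80%. None of the variants in the table brings the difference of differences to 80%.

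**Missing an added benefit is not the expected outcome.** A reader might infer that failure is likely even if .25 is real. For one comparison it is roughly a coin toss.

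**No decision rule equates non-significance with no benefit.** A reader might infer that the plan intends to declare the combination no better after a non-significant test. The article only lists that as one possible result, so the risk lies in interpretation.

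**Conclusion.** The point holds in a limited form. The .25 figure is right for a factor main effect or a within-arm change, and wrong for combined versus one single program, where power at .25 is about 51% and the detectable effect about .35 SD (63% and .31 if baseline-adjusted). For the interaction, the statement lacks a scale: as a difference of differences, power at .25 is about 29% and the detectable effect about .50 SD (36.5% and .43 if baseline-adjusted).

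These results rest on the article's 125 per arm and correlation of .5, and on the assumed two-sided 5% alpha, single pre-post change and no dropout. Dropout lowers all of them. This is not a complaint about detail that an article may leave to an analysis plan: it concerns a quantified statement that its own inputs do not support. The preceding sentence, on contrasts of treatment arms, has the same weakness wherever it is taken to mean one arm of 125 against another; the two should be corrected together and counted once.

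**What to change.** Limit the .25 SD statement to the factor main effects (250 v 250). Add that, with 125 per arm, correlation .5, two-sided alpha 5% (or whatever alpha was used), a single pre-post change and no dropout, the effects detectable with 80% power are about .35 SD for the combined arm against each single program and about .50 SD for the ISG-by-ITP interaction expressed as a difference of differences. Note that dropout makes these figures worse. If a half-scale interaction was intended, say so and give its equivalent as a difference of differences.

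Report the combined-minus-single differences and the interaction as estimates with 95% confidence intervals, and state that a non-significant result will not be read as showing that the combination is no better than the single programs.

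Status of the Trial indicates that all waves have been recruited, so the sample size is settled and this is a change of wording. The cost is a less favourable stated figure for a primary objective.

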## Discussion

To our knowledge this study is the first RCT of the effectiveness of a depression ISG, the first to systematically investigate if participating in a peer-to-peer ISG improves adherence and outcomes and the first to investigate the comparative effectiveness for rural and metropolitan consumers of an automated psychological intervention. In addition, there have been no previous studies of effect of an automated online self-help program on consumer empowerment.

A second novel contribution of this trial is its use of a purpose constructed plausible, web-based attention control containing authoritative information. At the time of writing, we were not aware of any published RCTs of the efficacy of e-mental health interventions which employed such a control. As already noted, depression or mental health education websites are not the preferred control condition for studies of interventions for mental disorders as there is evidence that such information may improve mental health. We did consider referring control group users to existing websites with a 'wellbeing' theme. However, these websites were typically characterised by one or a number of limitations in that they contained content that: included potentially active components (such as exercise interventions); incorporated advertisements, which raises ethical issues when used in the context of a research trial; were typically not evidence-based, a further ethical concern; might change or be removed from the Internet; and was not subject to the control of the research team. Moreover, external websites could not be seamlessly integrated into our automated research trial processes and accordingly it would not have been possible to automatically track trial participant access and usage of these sites.

### Status of the Trial

The trial was commenced in August 2008. Participants recruited in the pilot and wave 1 stages of the study have completed the 12-month follow-up. Participants recruited in the wave 2 stage have completed the 6-month follow-up with 12 month follow up due to be completed in May 2010.
